## Abstract

**Background:**

SPARCLE is a nine-centre European epidemiological research study examining the relationship of participation and quality of life to impairment and environment (physical, social and attitudinal) in 8–12 year old children with cerebral palsy. Concepts are adopted from the International Classification of Functioning, Disability and Health which bridges the medical and social models of disability.

**Methods/Design:**

A cross sectional study of children with cerebral palsy sampled from total population databases in 9 European regions. Children were visited by research associates in each country who had been trained together. The main instruments used were KIDSCREEN, Life-H, Strength and Difficulties Questionnaire, Parenting Stress Index. A measure of environment was developed within the study. All instruments were translated according to international guidelines. The potential for bias due to non response and missing data will be examined. After initial analysis using multivariate regression of how the data captured by each instrument relate to impairment and socio-economic characteristics, relationships between the latent traits captured by the instruments will then be analysed using structural equation modelling.

**Discussion:**

This study is original in its methods by directly engaging children themselves, ensuring those with learning or communication difficulty are not excluded, and by studying in quantitative terms the crucial outcomes of participation and quality of life.

Specification and publication of this protocol prior to analysis, which is not common in epidemiology but well established for randomised controlled trials and systematic reviews, should avoid the pitfalls of data dredging and post hoc analyses.

## Background

The International Classification of Functioning, Disability and Health (ICF) [1] takes account of the social model of disability [2] which considers disability to result from the interaction between individuals and their environment rather than being a characteristic of the individual. The ICF introduces Environmental Factors into its classification, defining them as the physical, social and attitudinal environment in which people live and conduct their lives. Theses factors include arrangements for educational provision, social attitudes and norms, legislation on access to buildings, anti-discrimination legislation, transport design, rehabilitation, therapeutic services and assistive technology.

Aspects of the environment in European countries are adapted to respond to the needs of the disabled child and their family; some being consistent across a country but varying considerably between countries. For instance, about one third of countries must provide wheelchair access to trains by law; whilst a different one third must allow such access to cinemas. There are also wide variations in financial benefits and availability of specialised services. The rationale for such arrangements arises from theoretical standpoints and from qualitative studies [3-5], but it is not known which are effective because they have rarely been evaluated against well-defined outcomes. For example the comprehensive review "What works in services for families with a disabled child?" [6] could only examine what parents thought they needed because of the lack of research-based evidence on the effectiveness of interventions. There is a need for high quality scientific evidence to inform national and European Union (EU) policies for disabled children.

This study uses two outcomes to assess effectiveness of provision for children with disability: an objective measure of what the child does – Participation; and a subjective measure of how the child feels – Quality of Life (QoL).

The ICF introduced the concept of Participation, defining it as involvement in life situations, with the following domains: learning and applying knowledge, general tasks and demands, communication, mobility, self-care, domestic life, interpersonal interactions and relationships, major life areas and community, social and civic life. The concept of Participation replaced that of handicap, introduced by the ICF's predecessor the ICIDH [7], which was rarely used in childhood because it was too medical and did not take sufficient account of the social construction of disability [8].

The WHO defines QoL as an individual's perception of their position in life in the context of the culture and value systems in which they live, and in relation to their goals, expectations, standards and concerns [9]. In particular it is a person's self reported, subjective account of their quality of life across a number of dimensions. This is sometimes called health related quality of life (HRQOL) with health referring to the WHO definition as a state of complete physical, mental and social wellbeing [10]. HRQOL also distinguishes it from concepts which include factors external to the person such as poverty, living in a police state, and wider environmental factors such as pollution [11]. HRQOL is also distinct from concepts such as functional disability or handicap [12] which a decade or more ago were sometimes called QoL.

Research on children's QoL used to rely on their parents' or other proxys' perceptions, but it is now appreciated that the child's view should, where possible, be sought directly rather than being inferred from proxy reports. Measurement of QoL in children has lagged behind that in adults because of concern about the reliability of children's self reports, and the different values they place on particular health states as compared to adults [13,14]. Early work developed measures for specific diseases such as cancer [15] and asthma [16] for the purpose of contributing to the evaluation of medical interventions, but there is now the need for generic measures which allow comparisons not only across children with different diseases states but also across children with and without impairments.

### Overall purpose and hypothesis

Although a number of qualitative studies asking disabled children and their families to report their experience have yielded important insights into the lives and views of such children [4,5], larger populations of disabled children now need to be studied quantitatively to determine how and why participation and quality of life vary between children with comparable severity of impairment. We are studying children with cerebral palsy (CP) because:

• CP is the commonest cause of significant motor impairment, occurring in 1 in 500 births or 10,000 new cases a year in the EU prior to recent enlargement.

• Children with CP often have impairments of learning, hearing, vision, communication and epilepsy in addition to their motor ones and so are representative of the wider population of disabled children.

• Children with CP are a group with relatively stable impairment where Participation and QoL will be influenced by social and educational environmental factors as well as by medical interventions.

• Adults with CP are disadvantaged in social relationships and employment [17,18] and children are disadvantaged in education, social relationships and employment prospects [3,19].

• There are population registers of such children, reducing the risk of bias in selection of cases.

• Children aged 8–12 years were targeted because they are much less studied than preschool children, can self-report their QoL and have not entered the adolescent stage where additional factors operate.

The principal hypothesis addressed is that children with similar severity of impairment will experience variable outcomes, in terms of Participation and QoL, due to variation in Environmental Factors.

As some Environmental Factors will be consistent across a country but vary between countries, the study should allow the identification of those Environmental Factors which, if improved, will yield the greatest benefits for children and their families. Such knowledge will be invaluable in informing EU policy in the health, educational and social sectors.

Pre-specification of randomised controlled trials [20] and systematic reviews [21] increases confidence in conclusions reached but is not common practice in epidemiology. The aims of this paper are to specify objectives, hypotheses and methods prior to data analysis; and so increase confidence in the validity of the conclusions by avoiding the pitfalls of data dredging and *post hoc *analyses [22].

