### Population

The names of the children eligible for the study are recorded on CP registers covering all children in defined geographical areas, each child classified for impairment by type and extent. The registers share the same definition of CP [23], include all severities of CP and make every effort to be comprehensive by receiving notifications from multiple sources. Fourteen centres with such registers form a collaboration [23], and eight of these centres joined the present study (Table 1): North England, West Sweden, Northern Ireland, South East France, South West Ireland, East Denmark, Central Italy, South West France. A further centre in North West Germany joined the study after the start and followed all study protocols; however its sample could not be drawn from a validated population database and was constructed from referrals from clinicians, statutory and voluntary bodies working with children with cerebral palsy in a defined geographic area.

In order to maximise numbers in the smaller centres, children with dates of birth between 31/7/1991 and 01/04/97 inclusive (i.e. between 7 years 3 months and 12 years 11 months on 1^st ^July 2004) were included with the oldest being approached immediately and the youngest not until near their eighth birthday.

As milder cerebral palsy is more common, in the centres with sufficient numbers (1, 6) we sought similar numbers of children at each severity level by grouping children into four strata by walking ability and selecting a random sample from each stratum. Centres 2 and 3 selected a random sample of children in the stratum of best walking ability and approached all children in the remaining strata. In the smaller centres (4, 5, 7, 8) all children were approached.

The target sample size in each stratum of walking ability was estimated from power calculations using Life-H scores of children with CP [24]. A change of 2 in mean Life-H score allows the most participatory children with severe impairment to achieve what many children with only moderately severe impairment achieve. It was estimated that 30 cases were needed in each stratum to detect a difference in mean scores of 2 and that the European collaboration could provide such numbers.

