To describe the environmental factors operating at a national or macro level, a review and search for relevant information was carried out by a social scientist. The results are available in an internal paper and include factors such as arrangements for educational provision, social attitudes, legislation on access to buildings, anti-discrimination legislation, transport design, rehabilitation, therapeutic services and assistive technology in the participating countries.

To describe the direct experience of environmental factors relevant to a particular child and family and the degree to which the environment helps or hinders, an instrument, the European Child Environment Questionnaire (ECEQ), was developed. Initial work included a literature review [32], and a qualitative study [33], followed by focus group work [34] in each country participating in SPARCLE. A domain structure was postulated on the basis of this qualitative work and is currently being verified using explanatory item response models [35].

As the Life-H instrument for participation does not capture frequency of participation for discretionary activities such as leisure, an instrument – the Frequency of Participation Questionnaire (FPQ) – was developed to capture frequency for those Life-H items for which it was meaningful. This was also administered to children in the general population in the relevant age range in each country to provide comparative normative data.

Translation of instruments followed international guidelines [36,37], with two forward translations and one backward one. A small amount of cultural adjustment was also needed concerning sporting activities, school types and parental socio-economic status. Table 2 details the translations undertaken.

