### Statistical methods

Data quality will be assessed, in particular: heterogeneity between centres, the potential for bias due to non-response and the extent and pattern of missing data. We will compare the proportions of children in these categories in each centre with the overall proportion using a relative risk function [38]. We will assess whether non-response was related to age, gender and level of impairment and whether any such associations can explain the differences in response rates between centres [39].

The psychometric properties of the data captured by the instruments in Table 2 will be compared with the properties reported by their developers. The following will be undertaken where relevant:

• Cronbach alpha for internal consistency, within countries and overall;

• Convergent/divergent validity by considering correlations between domains and/or correlation with a similar instrument;

• Confirmatory analysis to evaluate whether the underlying factors in the data are consistent with those which have been reported in reference populations.

A separate paper will be submitted for publication around each instrument describing these validations, summarising the data, comparing with similar studies and using multivariate linear or logistic regression to assess how scores on each domain vary with level and type of impairment and socio-economic characteristics. Due to sampling within strata defined by walking ability by some centres, all analyses will be adjusted for gross motor function. A further paper will compare parents' and children's assessments of the child's quality of life and explore the factors influencing the differences; and another paper explores whether severity of impairment can be represented by a single or possibly two latent variables.

As North West Germany did not ascertain their cases from a population-based register, all analyses will include a sensitivity analysis with and without this centre.

We are also very interested in how the concepts captured by the instruments vary between countries. We are still not sure whether to compare countries using fixed effect or random effect (equivalent to multi-level) models to allow for any residual correlation of responses within centres that is not explained by the recorded variables [40]. We will then explore whether residual differences between countries can be explained by factors operating at national level, as determined by the work of the social scientist described earlier.

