## Discussion

SPARCLE is a large, multi-centre study carried out in nine European centres. The results will be widely disseminated and it is essential that findings will be credible to academics in disability studies, social science, child health, psychology, to politicians and to developers of social, health and educational policy at national and European levels. This paper is an essential part of this process in that it sets out, prior to analysis, the background to the project, the concepts involved, the methods adopted and the analyses which will be undertaken.

There are a number of aspects to this study which have rarely been brought together in studies of children and disability. Wherever possible, the self-report of the child of their QoL has been obtained and used as the subjective outcome. However where children can not self report, they have been included but their QoL is reported by a proxy. The concept of Participation, introduced in the ICF and fully embraced by the European Commission's Research Frameworks is the other central measured outcome. The concept of the physical, social and attitudinal environment introduced by the ICF is also a crucial element of this study and an instrument to capture its experience by child and family has been specially developed. The environment at the national level is also being sought systematically and set out by a social scientist; and will allow the study to investigate the relationship of differences in environment between countries to differences in outcome between countries.

The study has a number of methodological strengths. It uses a network of population based registers of all children with CP living in defined geographic areas, from which either all children were included or children were randomly sampled; this allows thorough analysis of potential bias as registration data were known for those children whose families could not be contacted or who declined to take part. The questionnaires were translated according to international guidelines; the research associates who visited the children and families were trained together and adopted common procedures with common understanding; special attention was paid to data quality and completeness.

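### Seven countries cannot identify or rank environmental factors that are uniform within a country, so that part of the stated policy aim is unsupported

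*Protocol article*

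**What the plan says.** Under Overall purpose and hypothesis, the article reasons from national variation to a policy result. The sentence opens "As some Environmental Factors will be consistent across a country but vary between countries, the study should allow the identification of those Environmental Factors", and its conclusion in full is that "the study should allow the identification of those Environmental Factors which, if improved, will yield the greatest benefits for children and their families". It is worded as an expectation, and the article goes on to present such knowledge as input to EU policy. The Discussion repeats the national route more mildly: the review of national environments is to let the study relate differences in environment between countries to differences in outcome between countries.

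Under Instruments, a social scientist's review of national conditions is said to cover "factors such as arrangements for educational provision, social attitudes, legislation on access to buildings, anti-discrimination legislation, transport design, rehabilitation, therapeutic services and assistive technology". That is eight named kinds of factor, given as examples.

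Under Statistical methods, the matching analysis is described in one sentence: "We will then explore whether residual differences between countries can be explained by factors operating at national level". The same section leaves open whether countries enter as fixed or random effects, and requires every analysis to be run with and without North West Germany.

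The centres are listed under Population: "North England, West Sweden, Northern Ireland, South East France, South West Ireland, East Denmark, Central Italy, South West France", and then "A further centre in North West Germany joined the study after the start and followed all study protocols".

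There is also a second route. The ECEQ records the environment as each child and family experiences it, and the structural equation models that address the principal hypotheses are built by domain of the child's experience.

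**The concern.** A factor that is the same for everyone in a country takes one value per country. However many children are visited, its relation to outcome is estimated from as many points as there are countries. The stated aim is demanding: it is to say which factors, if changed, would help most. That requires separating factors from one another and ordering them. If the number of countries is close to or below the number of candidate factors, the data cannot do this, and no later analysis plan can add countries.

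At stake is what the study may conclude. The article is published to guard against data dredging, and its findings are meant for politicians and policy developers. An aim that the design cannot meet for national factors invites readers to treat an exploratory comparison of a few countries as evidence that a given law or service works.

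**Working it through.** **Plan's own figure.** The article gives none for national factors. Its only sample-size figure, 30 cases per walking-ability stratum to detect a difference of 2 in mean Life-H score, concerns children within strata and has no bearing on the number of countries.

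**Inputs.** From Population: UK (North England, Northern Ireland), France (South East, South West), Sweden, Ireland, Denmark and Italy make eight centres in six countries. Germany makes nine centres in seven countries. The sensitivity analysis without Germany leaves eight centres in six countries. From Instruments: at least eight kinds of national factor.

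**Step 1: how many factors can be separated.** With k countries and factors constant within country, the intercept and slopes together have rank at most k.
- k = 7: at most 7 − 1 = 6 slopes, with 7 − 1 − 6 = 0 residual degrees of freedom.
- k = 6: at most 5 slopes, again with 0 residual degrees of freedom.
- An intercept plus all eight named factors would be 9 parameters on a design of rank 7 (rank 6 without Germany), which is not identifiable.
- If fixed country effects are chosen, a country-constant factor is fully collinear with the country terms and cannot be estimated in the same model.

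**Step 2: one factor at a time.** The critical correlation is r = t/√(df + t²), with df = k − 2.
- k = 7: t(5) = 2.571, so r = 2.571/√(5 + 6.61) = 0.754.
- k = 6: t(4) = 2.776, so r = 2.776/√(4 + 7.71) = 0.811.

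Simulated two-sided 5% power, assuming a bivariate normal relation between factor and country mean:

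| Units | Critical absolute r | Power, true r = 0.5 | Power, true r = 0.7 | True r for 80% power |
|---|---|---|---|---|
| 6 | 0.811 | 17% | 37% | 0.894 |
| 7 | 0.754 | 21% | 46% | 0.856 |
| 8 (Northern Ireland counted apart) | 0.707 | 25% | 55% | 0.821 |
| 9 (every centre distinct) | 0.666 | 29% | 62% | 0.789 |

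Even if every centre counted as its own unit, only very strong relations would be seen.

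**Step 3: a yes/no national law.** The Background gives an example in which about one third of countries have a given access law. Taking 2 of 7 as an illustration, the smallest possible one-sided permutation p-value is 1/C(7,2) = 1/21 = 0.048. With 2 of 6 it is 1/C(6,2) = 1/15 = 0.067.

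**Step 4: ranking.** In simulation, eight mutually unrelated normal factors observed in seven countries have a median largest pairwise absolute correlation of 0.82. Chance overlap of this size means that single-factor results could not be told apart.

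**Step 5: why the error term matters (illustration only).** Suppose a national factor were tested against child-level error, with an assumed 60 children per centre. The design effect is 1 + 59 × ICC, and the true type I error is 2 × (1 − Φ(1.96/√design effect)). For an assumed residual ICC of 0.01, the design effect is 1.59 and the error about 12%. For 0.05 it is 3.95 and about 32%. For 0.10 it is 6.90 and about 46%. The article does not say it will test this way, and neither input is in the document.

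**The case against.** The strongest reply is that the plan claims less than a critic may read into it. The aim is worded as an expectation, the national analysis is called exploratory, and the Discussion speaks only of investigating a relationship. The list of eight factors describes what a review covered. Nothing says that all eight enter one model, that each is tested at 5%, or that each is constant within a country. Coding and limiting the factors is work a fuller analysis plan commonly does. The main route to the principal hypotheses is the child-level ECEQ with structural equation models, which does not depend on the number of countries in this way.

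Most of this stands, and it rules out two stronger readings.

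- A reader might infer that the study cannot identify environmental factors at all. The documents do not support that. Factors that vary between children within a country are measured by the ECEQ and are open to study.
- A reader might infer a known false-positive rate, such as 1 − 0.95⁸ = 34% for eight independent tests, or 32% for a test against child-level error. Neither analysis is planned. Random effects are under consideration precisely to allow for correlation within centres, and the 32% is one point in the 12% to 46% range above.

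What does not stand is the suggestion that softer wording or a later plan removes the problem. The sentence in the purpose section derives its aim from factors uniform within a country. For those, the limit is the number of countries, and the aim exceeds the exploratory analysis offered for it.

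**Conclusion.** The point holds in a limited form. For factors constant within a country, the design offers seven observations (six without Germany), which cannot separate or rank the factors and give little power even for one. The expectation that such factors can be identified by their benefit is therefore a property the design does not have.

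The count of countries and the rank limit follow directly from the centre list. The critical correlations assume an ordinary two-sided 5% test on country means, and the power figures also assume normality. The result is not sensitive to whether Northern Ireland is counted apart.

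The outcomes, the sampling and the main structural equation analysis are unaffected. This is a claim to correct, because it governs what may be concluded about national policy. It is not a flaw in the study as a whole.

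**What to change.** 1. **Overall purpose and hypothesis, and the echo in the Discussion.** Limit the identification claim to child- and family-level factors measured by the ECEQ and analysed in the structural equation models. State that factors uniform within a country can be compared only descriptively across seven countries.
2. **Statistical methods.** Label the comparison of national factors descriptive or hypothesis-generating, with no ranking and no claim that a factor is effective. Plotting adjusted country means against a factor would suffice.
3. **Any test of a national factor.** Base it on between-country variation with country-level degrees of freedom, for example a second-stage regression of adjusted country means, and not on child-level error. Show it with and without Germany.
4. **Optional.** If one summary test is wanted, pre-specify a single composite national index per outcome.

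The cost is some wording and a simple second-stage analysis, with no new data. The downside is a more modest policy claim.
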